#### MRI data

Quality of BOLD fMRI data will be extensively checked, before data will be pre-processed according to standard recommended procedures. Subsequently, data will be modelled on the subject level using onsets/duration for the different task conditions, or time-course information. On the second level, between-group comparisons will be performed in order to analyse residual abnormalities in emotion regulation capacity, verbal working memory performance and resting state-perfusion and functional connectivity. A multilevel analysis model will be set up to test for the effects of treatment on these measures. Furthermore, linear modelling will be applied to identify and test the predictors of long-term treatment success, as defined by symptomatology (at T0, T1, T2) and relapse status and course (T1-T2) in the larger sample of remitted patients who have received therapy. Multivariate pattern analysis will be performed to evaluate the predictive value of post-treatment characteristics and pre-treatment changes for long-term treatment success. Effects will be considered significant at *p* < .05, corrected for multiple comparisons.

#### Pupillometry data

Pupillometry data will be corrected for eye blinks and modelled to task data. Summary statistics will be entered in (Repeated Measures-)AN(C) OVAs, multi-level models and linear regression models. Effects will be considered significant at *p* < .05 after appropriate correction for multiple comparisons. To investigate whether PDR measurements have value for predicting frontal brain activation during emotion regulation, the PDR will be related to functional activation of regions implicated in effortful emotion regulation using multiple regression, while controlling for the arousal component of the sympathetic response, in the form of variation in SCR and HRV.

To investigate whether these relations are unique for effortful emotion regulation, linear regression models of the PDR during effortful emotion regulation (ERT) and during working memory (VWMT) will be set up and compared. Finally, it will be investigated whether treatment success can be predicted from multivariate patterns based on information from different modalities.

## Discussion

The high prevalence of recurrence in MDD poses a major clinical challenge and requires a better understanding of relapse vulnerability and of factors underlying preventive therapy success [108]. Recent reports explicitly call for combined neuroscientific and clinical research to improve current treatment [8, 109, 110]. The NEWPRIDE trial will be the first to study working mechanisms and predictors of Preventive Cognitive Therapy by examining neurophysiological and cognitive processes associated with attentional processing and regulation of both positive and negative emotional information.

In this RCT, we examine vulnerability for relapse by comparing pre-treatment neurocognitive processing in rrMDD with a group of HC, and we investigate hypothesized changes induced by PCT as compared to a waiting list control condition. Clinical, cognitive, and fMRI assessments in the remitted patient group are performed immediate and 15 months after treatment, to gain insight in the working mechanisms of preventive cognitive therapy and to examine predictors of relapse and relapse prevention.

One of the main strengths of the present study is the composition of the patient sample: only highly recurrent remitted MDD patients are included, allowing for the thorough examination of relapse mechanisms. Furthermore, given the expected relapse rate of 50% within 1,5 years follow-up, the relatively high recurrence in the present sample makes it possible to study predictors of (prevention of) relapse. The lack of confounding antidepressant medication use, recent cognitive therapy use, or current comorbid psychiatric diagnoses makes for a clean examination of residual characteristics and therapy effects. Another strength is the thorough investigation of clinical and neurocognitive features in this study, providing a broad and extensive investigation of mechanisms facilitating vulnerability and prevention of relapse.

A methodological difficulty of the follow-up design is the risk of participants dropping out, a risk enlarged by the expected amount of relapse. If possible, participants who drop out will be replaced. For the longitudinal analysis, the number of included participants will be sufficient to allow for an estimated 20% loss of participants and to detect an expected medium-sized within-group treatment effect. Furthermore, the fact that the last group of participants is scanned on a different MR-scanner might lead to higher between-group variance. Fortunately, the scanner change only affects the longitudinal analyses of PCT success prediction in the treatment condition. Since we anticipate a 50% relapse in both first-scanner and second-scanner participant group, and because pre- and post-treatment scanning is performed on the same scanner in all participants, we expect that any effect of the scanners will be equally divided between the relapse- and no-relapse groups, thereby minimizing possible limiting effects of the scanner change.

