### Aims

In the Neurocognitive Working Mechanisms of the Prevention of Relapse In Depression (NEWPRIDE) study, the neurocognitive mechanisms of preventive therapy will be investigated using a within-subject longitudinal comparison of cognitive biases and fMRI characteristics related to positive and negative emotion processing before and after PCT, as compared to a waiting list control group. At baseline, a healthy control (HC) group will be included for cross-sectional comparison of residual abnormalities.

The present study has four main aims. Firstly, we aim to cross-sectionally examine whether cognitive biases and functional magnetic resonance imaging (fMRI) responses during the regulation of positive and negative emotions in medication-free, highly recurrent, remitted MDD (rrMDD) patients differ from controls. We hypothesize residual abnormalities in rrMDD patients compared to HC in (i) an amygdala-insular-subgenual anterior cingulate cortex (ACC)-ventrolateral prefrontal cortex (PFC) circuitry associated with biased processing of negative emotional information, (ii) a striatal-medial PFC circuitry associated with biased processing of positive emotional information, and (iii) the lateral-and medial PFC circuitry associated with cognitive control [75].

Secondly, this randomized controlled fMRI-study is the first to investigate the neurocognitive working mechanisms of PCT (compared to a waiting list condition) in rrMDD patients. We hypothesize that PCT will result in increased lateral and medial prefrontal activation, dampened activation of limbic regions, and improved connectivity between these regions during emotion regulation, which will coincide with normalised processing and regulation of negative information and a lowered likelihood of a prevailing negative mood. Furthermore, we hypothesize that increased PFC activation following PCT relates to increased preferential processing of positive information [70, 76].

Thirdly, we aim to identify pre-treatment neurocognitive markers predictive of long-term PCT success measured at 18-month follow-up. It is expected that low pre-treatment insular and PFC activation [39, 77] and low PFC connectivity with emotion processing areas during emotion processing predicts favourable treatment response [78]. Also, we hypothesize that participants with larger pre-post differences on neurocognitive measures, will show lowest relapse up until18-month follow-up.

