#### Sample size

A total of 100 participants will be included, of which 75 rrMDD patients and 25 HCs. Power analyses for behavioural data, performed with G*Power 3.9.1.4, show that groups of 25 are sufficient to detect moderate effects (with 80% power and α = 0.05) for both cross-sectional group comparisons and longitudinal treatment effect analyses. Exact power analyses for fMRI analyses are difficult, due to the complex mass univariate nature of the data. However, previous comparable imaging studies yielded sufficient power with the inclusion of 20 participants per group [21, 37, 64, 70, 78, 82, 83]. We will include a minimum of 25 (carefully selected) participants per group, to allow for loss of data due to follow-up drop-outs.

The inclusion of 75 rrMDD patients allows for several lines of analysis. Firstly, cross-sectional comparisons will be carried out in 50 rrMDD patients versus 25 HCs in order to establish residual abnormalities in emotion processing. Because of an (unforeseen at the time of planning of the study) replacement of the MRI scanner, the last included 25 rrMDD patients (all allotted to the treatment condition) will be scanned on a different scanner, and will therefore not be included in this analysis. Secondly, longitudinal analyses of immediate treatment effects will be performed in the first 50 rrMDD patients who were randomized to either the therapy group or the waiting list control (25 vs. 25). Finally, since it is expected that 50% of rrMDD patients relapses within 1,5 years [41, 59], an additional group of 25 rrMDD patients will be included for the PCT condition, expanding the group of participants receiving treatment to *n* = 50 to allow analyses of pre-post differences in relation to clinical outcome at 18-month follow-up. Even though these last 25 patients will be scanned on a different MRI scanner, we will ensure that all participants have their pre- and post-treatment scanning session on the same MR machine.

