### Measures

#### Primary outcome measures

The primary outcome of the cross-sectional assessment of rrMDD characteristics is threefold: it concerns baseline characteristics at T0 in (i) cognitive biases to negative and positive emotional information (measured with the Attentional Response to Distal vs. Proximal Emotional Information task (ARDPEI) [86], an adapted version of the Emotional Reasoning Task [87] and an Implicit Association Task (IAT) [88]); in (ii) blood oxygenation level dependent (BOLD) response (during an Emotion Regulation Task (ERT) (similar as in [81, 89]), a Verbal Working Memory Task (VWMT) [90], and during resting state; and in (iii) the PDR during these neurocognitive tasks.

Changes in these measures following PCT at T1 are the main study parameters in the assessment of the working mechanisms of PCT. The primary outcome for the assessment of treatment predictors concerns (i) depressive symptomatology, as measured with the Inventory of Depressive Symptomatology self-report version (IDS –SR30) [91] at T0, T1 and T2, and (ii) time to relapse and number of relapse over the course of the study, as measured with the Structured Clinical Interview for DSM-IV disorders (SCID-I) [92] at T1 and T2, in combination with the life chart method at T2.

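### Sample adequacy for the longitudinal analysis is claimed for a within-group effect, although the randomised question is the PCT versus waiting-list difference in change

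*Protocol article*

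**What the plan says.** The treatment-effect question is set between arms. The Aims section describes a longitudinal comparison "before and after PCT, as compared to a waiting list control group", and its second aim concerns the "neurocognitive working mechanisms of PCT (compared to a waiting list condition) in rrMDD patients". The Sample size section places the analysis of immediate treatment effects in the first 50 patients, "randomized to either the therapy group or the waiting list control (25 vs. 25". The Randomization section says those 50 are randomised so that immediate PCT effects can be analysed, and the Discussion again names the waiting list as comparator.

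Two statements claim that the numbers suffice. The Sample size section says of the behavioural data that "groups of 25 are sufficient to detect moderate effects (with 80% power and α = 0.05". It applies this to the baseline comparison with controls and to the longitudinal analysis alike; the test and the numerical effect are not given. The Discussion says the number for the longitudinal analysis covers a 20% loss and is enough "to detect an expected medium-sized within-group treatment effect".

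Under Primary outcome measures the mechanism outcome carries no comparator: "Changes in these measures following PCT at T1 are the main study parameters in the assessment of the working mechanisms of PCT".

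**The concern.** A mean change within the PCT arm and a difference in mean change between arms are different quantities with different precision. With n patients per arm and equal variances, the between-arm difference in change has √2 times the standard error of one arm's mean change. It equals the within-PCT change only if the waiting list does not move. Enough patients for a medium change within one arm is therefore not enough for a medium difference between arms.

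At stake is how a null result will be read. If the between-arm comparison is not significant, a reader of the Discussion may take it as the outcome of a test sized for a medium effect with loss already allowed for. For the randomised contrast, the article does not show that.

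**Working it through.** **Inputs from the article.** 25 per arm; 20% loss, so 25 × 0.8 = 20 per arm; 80% power; α = 0.05; effect described only as moderate or medium.

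**Assumed, because not given.** Two-sided test; medium = 0.5 SD of change, or f = 0.25 in a repeated-measures ANOVA; pre-post correlation ρ = 0.5, range 0.3 to 0.7. At ρ = 0.5 the SD of change, √(2(1 − ρ)) raw SD, equals the raw SD.

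**Step 1: the article's own figure.** It cannot be reproduced uniquely, since the test is not named.
- Paired t, 0.5 SD of change, two-sided: noncentrality 0.5√n, which is 2.50 at n = 25 and 2.24 at n = 20. Power is 67% and 56%; 80% needs n = 34.
- The same test, one-sided: 78% at n = 25 and 70% at n = 20; 80% needs n = 27.
- Repeated-measures ANOVA, two groups and two occasions, f = 0.25, ρ = 0.5: λ = f² × N × 2/(1 − ρ), which is 12.5 at N = 50 and 10 at N = 40. Power is 93% and 87%. At ρ = 0.3 it is 83% and 74%.

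So 25 per group can be called sufficient under some standard settings and not under others.

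**Step 2: the randomised contrast.** Two-sample t on change, noncentrality d√(n/2), two-sided 0.05.

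| Per arm | Noncentrality at d = 0.5 | Power at d = 0.5 | d for 80% power |
|---|---|---|---|
| 25 | 1.77 | 41% | 0.81 |
| 20 | 1.58 | 34% | 0.91 |

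Power of 80% at d = 0.5 needs 64 per arm. One-sided, power is 54% and 46%. The within-arm test has 80% power for 0.58 SD at n = 25 and 0.66 SD at n = 20, so the between-arm requirement is about 1.4 times larger (0.81/0.58; 0.91/0.66).

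**Step 3: baseline adjustment.** For a difference of 0.5 raw SD, the standardised effect is 0.5/√(2(1 − ρ)) for change scores and 0.5/√(1 − ρ²) for ANCOVA.

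| ρ | Change score, 25 per arm | ANCOVA, 25 per arm | ANCOVA, 20 per arm |
|---|---|---|---|
| 0.3 | 0.310 | 0.443 | 0.365 |
| 0.5 | 0.410 | 0.516 | 0.429 |
| 0.7 | 0.609 | 0.679 | 0.578 |

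None reaches 0.80. With ANCOVA and 20 per arm, the detectable difference at 80% power is about 0.909 × √(1 − ρ²), that is 0.87, 0.79 or 0.65 raw SD.

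**Step 4: what f = 0.25 means for the arm-by-time term.** In a two-by-two layout a difference in change δ puts ±δ/4 into each cell, so f = δ/(4 × SD) and f = 0.25 gives δ = 1.0 raw SD. At ρ = 0.5 the two-sample test on change with d = 1.0 and 25 per arm has squared noncentrality 1.0² × 25/2 = 12.5, the λ of Step 1. The 87% at N = 40 is therefore power for a difference twice the conventional 0.5 SD.

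**The case against.** **The contrast itself is clear.** A reader might infer from the words within-group, and from the missing comparator under Primary outcome measures, that a PCT-only pre-post change could decide the mechanism question, with retest change then counted as a PCT effect. The article does not support this. The Aims, Sample size, Randomization and Discussion sections all point to PCT against waiting list, and no section plans a PCT-only test of efficacy. The outcome sentence names a variable; the model term can properly sit in an analysis plan that is not shown. This objection stands, and the point is confined to the power basis.

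**The stated power cannot be proved wrong.** A reader might also infer that the 80% claim is false. Test, sidedness, effect and correlation are unstated, and the f = 0.25 setting supports 25 per group. That stands too, but that setting does not describe a 0.5 SD difference between arms.

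**The sentence may concern another analysis.** The same paragraph of the Discussion mentions predicting PCT success within the treatment condition. In those 50 patients, or 40 after loss, a 0.5 SD within-group change has 93% or 87% power. This reading is possible but less natural: relating change to relapse is prediction, and the Sample size section uses treatment effects for the randomised 50. On this reading the Discussion would say nothing about adequacy of the randomised comparison after loss.

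**34% is a low choice.** It assumes completers only and no baseline adjustment, whereas dropouts are to be replaced if possible and multilevel models are planned. That is fair; the more favourable figures of 44% to 68% at 25 per arm are still short of 80%.

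**Conclusion.** The point holds as a mismatch between the sufficiency claim and the randomised contrast. The Discussion rests adequacy after 20% loss on a medium within-group effect, while the trial randomises 25 versus 25 to estimate a between-arm difference in T0–T1 change. For a difference of 0.5 SD of change, between-arm power is 41% at 25 per arm and 34% at 20. The design has 80% power only for about 0.81 or 0.91 SD.

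These sizes rest on the assumed meaning of medium, a two-sided 0.05 test and an unadjusted change score. Baseline adjustment over correlations of 0.3 to 0.7 moves the figures but not the conclusion. They concern a single behavioural outcome; the correction for multiple comparisons planned for imaging and pupillometry is not included.

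**What to change.** - **Discussion, paragraph on drop-out:** replace the within-group effect with the PCT versus waiting-list difference in T0–T1 change that 20 per arm can detect. State the effect-size scale, the assumed pre-post correlation, the sidedness and whether baseline is adjusted for. For an unadjusted two-sided test this is 0.91 SD of change. Do not describe the sample as sufficient for a medium (0.5 SD) between-arm effect.
- **Sample size:** put the longitudinal half of the power statement on the same basis, naming the test. If f = 0.25 for the arm-by-time term was used, say that it corresponds to a difference in change of 1.0 raw SD.
- **Primary outcome measures:** add that change following PCT is compared with waiting list.
- **If the Discussion sentence was meant for the 50 PCT patients only,** say so, and give the between-arm figure separately.

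This changes wording only; design, sample and analysis stay as they are. The cost is a less favourable stated detectable effect.

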#### MRI procedure

MRI scanning will be performed on two scanners (due to an unforeseen scanner replacement). The 25 HC and the first 50 rrMDD subjects will be scanned on a Philips Intera 3 Tesla MR system, equipped with a 32-channel receiver head coil, at the NeuroImaging Center, University Medical Center Groningen. The last 25 rrMDD patients (all in the treatment condition) will be scanned on a Siemens 3 Tesla Magneton Prisma MR system (equipped with a 64-channel receiver head coil), at the Radiology Department of the University Medical Center Groningen, using imaging protocols harmonized to the Philips protocols.

The scanning procedure involves two functional echo planar imaging (EPI)-based acquisitions (TR/TE 2000/30 ms, 90° flip angle, voxel size 3.5 × 3.5 × 3.5 mm) to measure BOLD contrast during the ERT and the VWMT, one functional EPI-based acquisition (TR/TE 2000/30 ms, 70° flip angle, voxel size 3.5 × 3.5 × 3.5 mm) sensitive to BOLD contrast during rest (RS), one T1-weighted structural scan for anatomical reference (TR/TE 9/3.5 ms, 8° flip angle, voxel size 1x1x1mm), and finally a pseudo-continuous arterial spin labelling (pCASL) acquisition (TR/TE 2000/14 ms, 90° flip angle, voxel size 3x3x3).

During the ERT, VWMT and RS acquisitions, simultaneous pupillometry will be recorded using an SR-Research MR-compatible Eyelink system (Mississauga, Canada). Besides changes in brain activation and pupil dilation, autonomic responses to emotional events and stimuli include increased skin conductance reactivity (SCR) and changes in cardiovascular activity (HRV) [107]. We will measure SCR during MRI scanning using an MR-compatible Direct Current Galvanic Skin Response MR sensor interfaced with the BrainAmp ExG MR amplifier (Brain Products, GmbH) by applying a constant voltage (.5 V) between two sintered Ag/AgCl electrodes attached to the palmar surface of the distal phalanges of the index and middle fingers of the left hand. Furthermore, HRV signal will be recorded during scanning, logging the R-top trigger produced by the standard cardiac equipment of the Philips and Siemens MRI systems. In order to correct for additional noise, respiratory rate and depth will be measured through pressure variation in a cushion that is fastened around the participant’s abdomen. Finally, before every fMRI acquisition, the state tension levels of the participant will be monitored, by asking them how tense they feel on a Visual Analogue Scale.

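### Expected balance of relapse across scanners does not justify pooling the 50 PCT patients without a scanner adjustment, and the scanner exclusion in the cross-sectional comparison is not limited to imaging

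*Protocol article*

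**What the plan says.** - **Who is scanned where.** MRI procedure: all 25 healthy controls and the first 50 patients use the Philips system with a 32-channel coil. "The last 25 rrMDD patients (all in the treatment condition) will be scanned on a Siemens 3 Tesla Magneton Prisma MR system", with a 64-channel coil and protocols harmonised to the Philips ones. Of the first 50, 25 receive PCT, so the pooled PCT sample is 25 per machine.
- **How the prediction analysis is defended.** The Discussion allows that the second machine may raise between-group variance. It then argues from an anticipated 50% relapse on each machine, and from scanning each patient twice on the same machine, that "we expect that any effect of the scanners will be equally divided between the relapse- and no-relapse groups". It also limits the reach of the change: "Fortunately, the scanner change only affects the longitudinal analyses of PCT success prediction in the treatment condition".
- **How it is modelled.** The MRI data section plans linear models and multivariate pattern analysis in the enlarged treated sample and names no scanner adjustment. Age, sex and education are named as covariates, but under questionnaire and behavioural data.
- **What is predicted from what.** The third aim (Aims) looks for pre-treatment markers, such as low baseline insular and prefrontal activation and low prefrontal connectivity. As a further hypothesis it relates pre-post differences to relapse.
- **The cross-sectional comparison.** Sample size: "cross-sectional comparisons will be carried out in 50 rrMDD patients versus 25 HCs". The last 25 patients "will be scanned on a different scanner, and will therefore not be included in this analysis". The sentence does not separate imaging from other outcomes, although the primary outcomes of this comparison include "cognitive biases to negative and positive emotional information".

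**The concern.** Balance between relapse and no-relapse groups in expectation is not balance in the one trial that is run, and neither kind of balance removes variance that the scanner adds. The same-machine safeguard works within a patient. A baseline marker is compared between patients, half of them measured on a different vendor's machine with a different coil. The stated reasoning therefore leaves the first-named hypotheses of the third aim unprotected and, taken at its word, argues against adding the adjustment that would protect them.

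The second part is an inconsistency of scope. A scanner-based reason removes 25 patients from primary cognitive-bias outcomes that are not measured in the scanner, while the Discussion says that only the prediction analyses are affected. At stake are power for the imaging predictors of relapse, some precision in a primary cross-sectional comparison, and a correct account of what the scanner change touches.

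**Working it through.** **The plan's own figures.** The article gives no figure for a scanner effect or for the pooled prediction analysis. Its only power statement is that "groups of 25 are sufficient to detect moderate effects (with 80% power and α = 0.05". Reading moderate as d = 0.5, two-sided, 25 vs 25 gives 41% power, and the effect detectable with 80% power is d = 0.81; the statement is not reproduced for the cross-sectional case. For the longitudinal case it is met under f = 0.25 and an assumed correlation of 0.5 (93% at N = 50). That is a separate matter, and nothing below depends on it.

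**Inputs.** From the documents: 25 PCT patients per scanner, 50% expected relapse on each, 25 controls, 50 or 75 patients. Assumed, because the documents give no value: a scanner shift of s within-scanner SDs (0 to 1 as the main range, 2 as an extreme) and a true relapse/no-relapse difference of 0.8 SD in a marker.

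**1. Chance imbalance.** Take X and Y independent Binomial(25, 0.5).
- P(|X − Y| ≥ 3) = 48%
- P(|X − Y| ≥ 5) = 20%
- P(|X − Y| ≥ 7) = 6.5%

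With 20 per scanner (20% loss), a difference of 5 or more has probability 15%. When the split is 10 vs 15, 15/25 of relapsers but 10/25 of non-relapsers were scanned on the second machine. An unadjusted contrast is then displaced by (0.60 − 0.40) × s = 0.20 SD per SD of shift.

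**2. Variance under perfect balance.** With two equal scanner groups, total variance = 1 + s²/4.
- s = 0.5: 1.0625
- s = 1: 1.25, so effective sample size falls by 1 − 1/1.25 = 20%
- s = 2: 2.0

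**3. Power and type I error.** Linear model of the marker on relapse, 25 patients per scanner, 6,000 simulated trials per setting (Monte Carlo SE of a power near 78%: √(0.78 × 0.22/6000) ≈ 0.5 points).

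| Shift s | Power at 0.8 SD, no term | Power, with term | Type I, 50%/50% relapse, no term | Type I, 40%/60% relapse, no term | Type I, 40%/60%, with term |
|---|---|---|---|---|---|
| 0 | 78% | 77% | 4.7% | 4.8% | 5.0% |
| 0.5 | 76% | 78% | 5.1% | 6.1% | 4.8% |
| 1 | 69% | 78% | 4.7% | 9.5% | 4.9% |
| 2 | 49% | 77% | 5.3% | 17.9% | 4.9% |

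With truly equal rates the displacement in step 1 averages out over trials, so the loss is in power. Inflation appears only where the true relapse rates differ by scanner.

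**4. What same-machine scanning protects.** Let a patient's measurement be m + s on the second scanner. The change score is (m₁ + s) − (m₀ + s) = m₁ − m₀, so an additive shift cancels. The baseline value m₀ + s keeps it. The Aims section uses both kinds of predictor.

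**5. The cross-sectional exclusion.** The Overall procedure section places ARDPEI and IAT (with their own eye tracker), the Emotional Reasoning Task and the questionnaires outside the MRI session. For these measures:
- SE ratio, 75 vs 25 against 50 vs 25: √[(1/75 + 1/25)/(1/50 + 1/25)] = 0.943, about 6% smaller
- power at d = 0.5, two-sided: 52% to 57%
- effect detectable with 80% power: d = 0.70 to 0.65

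The gain is modest because the 25 controls are the limiting group.

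**The case against.** The article is a condensed account. Its imaging section lists no covariates at all, so a reader might infer that scanner will be left out of the models. The documents do not say so, and a full protocol or SAP could include it. That stands. What remains is the reason the article does give, which is insufficient whatever a later document adds.

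Protocols are harmonised, so the shift may be small; at 0.5 SD the loss is about two points of power. Much of the case for enlarging the PCT group rests on pre-post differences, for which an additive shift does cancel. Both points stand and limit the size of the concern, but neither covers the baseline predictors.

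A reader might also infer that the scanner change is handled the wrong way round. It is not. Every control was scanned on the first machine, so leaving the last 25 patients out of the fMRI comparison is correct. Leaving them out of PCT versus waiting list is also correct, because they were not randomised. In-scanner pupil data may depend on the set-up, so scanner is not clearly irrelevant there.

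Finally, one common sample across the three primary modalities is defensible, and the later patients differ in enrolment period. That argues for a sensitivity analysis. It is not the reason that the article gives, which is the scanner.

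**Conclusion.** The concern holds in a limited form. The balance argument does not neutralise the scanner change in the pooled 50-patient analysis: sizeable chance imbalance is common, the added variance remains, and baseline activation and connectivity predictors are not protected by same-machine scanning. Without a scanner term, power for a 0.8 SD difference goes from about 78% to about 69% as the assumed shift goes from 0 to 1 SD; with the term it stays at about 77-78%. The shift is an assumption, and a small one would cost little. The figures do not support a claim of inflated type I error in general: that needs relapse rates that truly differ by scanner, for example 40% vs 60%, where it reaches about 10% at 1 SD.

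The cross-sectional exclusion is right for fMRI but drawn too widely. It also sits badly with the Discussion's statement that only the prediction analyses are affected. Even if that statement is meant as a remark about scanner noise alone, the change still costs the cross-sectional comparison 25 patients. Correcting this brings about 5 points of power at d = 0.5, so it is the lesser of the two parts.

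**What to change.** - Include scanner as a fixed factor in every imaging model that pools the 50 PCT patients, including any that relate pupil response to BOLD in that sample.
- In the multivariate pattern analysis, handle scanner within the training folds (for example, standardise features by scanner there).
- Limit the exclusion in Sample size to fMRI and other in-scanner measures. Use 75 patients vs 25 controls for the cognitive-bias tasks, questionnaires and out-of-scanner pupil data, with 50 vs 25 as a sensitivity analysis for enrolment period.
- Keep the last 25 patients out of PCT versus waiting list.
- In the Discussion, replace the claim of equal division with a statement that scanner is adjusted for, and why change scores and baseline values differ in exposure. Correct the statement on which analyses are affected.

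Cost: wording, and one degree of freedom per model. If there is no scanner shift, the term costs about one point of power (78% to 77%). No new data are needed.
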